## Abstract

**Background:**

Dementia disease is a chronic condition that leads a person with dementia (PwD) into a state of progressive deterioration and a greater dependence in performing their activities of daily living (ADL). It is believed nowadays that PwDs and their informal caregivers can have a better life when provided with the appropriate services and support. Connected Health (CH) is a new technology-enabled model of chronic care delivery where the stakeholders are connected through a health portal, ensuring continuity and efficient flow of information. CH has demonstrated promising results regarding supporting informal home care and *Aging in Place*, and it has been increasingly considered by researchers and health care providers as a method for dementia home care management.

**Objective:**

This study aims to describe the development and implementation protocol of a CH platform system to support informal caregivers of PwDs at home.

**Methods:**

This is a longitudinal observational mixed methods study where quantitative and qualitative data will be combined for determining the utility of the CH platform for dementia home care. Dyads, consisting of a PwD and their informal caregiver living in the community, will be divided into 2 groups: the intervention group, which will receive the CH technology package at home, and the usual care group, which will not have any CH technology at all. Dyads will be followed up for 12 months during which they will continue with their traditional care plan, but in addition, the intervention group will receive the CH package for their use at home during 6 months (months 3 to 9 of the yearly follow-up). Further comprehensive assessments related to the caregiver’s and PwD’s emotional and physical well-being will be performed at the initial assessment and at 3, 6, 9, and 12 months using international and standardized validated questionnaires and semistructured individual interviews.

**Results:**

This 3-year funded study (2016-2019) is currently in its implementation phase and is expected to finish by December 2019. We believe that CH can potentially change the PwD current care model, facilitating a proactive and preventive model, utilizing self-management–based strategies, and enhancing caregivers’ involvement in the management of health care at home for PwDs.

**Conclusions:**

We foresee that our CH platform will provide knowledge and promote autonomy for the caregivers, which may empower them into greater control of the care for PwDs, and with it, improve the quality of life and well-being for the person they are caring for and for themselves through a physical and cognitive decline predictive model. We also believe that facilitating information sharing between all the PwDs’ care stakeholders may enable a stronger relationship between them, facilitate a more coordinated care plan, and increase the feelings of empowerment in the informal caregivers.

**International Registered Report Identifier (IRRID):**

DERR1-10.2196/13280

## Introduction

### Background

Dementia is a neurodegenerative chronic condition that is frequently described as a clinical syndrome characterized by cognitive and functional decline accompanied by changes in a person’s behavior and personality, which interferes with social or occupational functioning [1]. As the World Health Organization (WHO) reports, an estimated 47 million people worldwide were affected in 2015, and these numbers are expected to increase to 75 million by 2030 and 132 million by 2050 [2]. This was one of the main reasons for the WHO to designate dementia as a public health priority in 2012 [3], launching a public health dementia plan in 2017 [2]. Dementia is considered one of the most disabling chronic diseases that leads the person with dementia (PwD) into a state of progressive deterioration and a greater dependence in performing their activities of daily living (ADLs).

A dementia diagnosis also has a significant impact on the PwD’s family who often bear the responsibility of caring for them as their condition progresses. Family members, usually a spouse or a child, are often referred to as *informal caregivers*, as they provide unpaid and continuous assistance contrary to formal caregivers who are paid for their professional services [4]. Informal caregiving can help to maintain the PwD at home, avoiding institutionalization and providing the *Aging in Place* new model of care, which consists of helping older people to remain living at home for as long as possible; avoiding nursing home placement; and contributing to an increase in well-being, independence, social participation, and healthy aging [5]. However, along with the well-being and economic improvement that *Aging in Place* can offer, previous research has also shown that the majority of people older than 75 years prefer living independently at home for as long as possible [6].

Although it is recognized that dementia can bring many challenges for the PwDs and their caregivers, it is also believed that nowadays they can have a better life when provided with the appropriate diagnosis and the proper services and support [7]. Connected Health (CH) is a new technology-enabled model of chronic care delivery where the stakeholders are *connected* through a health portal, ensuring continuity and efficient flow of information [8]. CH has demonstrated promising results regarding supporting informal home care and *Aging in Place* [9,10]. It represents an opportunity for passive and unobtrusive home monitoring, and increasingly, it is being considered by researchers and health care providers to be an enabler for dementia home-based health and wellness measurement and monitoring using mobile devices for storage, update, and transmission of patient data. The data captured from everyday life in PwDs can be of great value when put in the hands of the appropriate stakeholders, such as the health care professionals and the informal caregivers, as it can help to track the progress of PwDs and act as a predictor of any cognitive or physical decline [11]. Furthermore, reductions in PwD’s caregiver burden, stress, depression, and anxiety as well as improved self-efficacy and confidence regarding caregiving skills have also been found; hence, it is believed that these results can be extrapolated to PwDs and that the implementation of these technologies may then improve the quality of life for both the PwD and their caregiver [12].

In terms of technology-driven interventions for dementia care, recent research shows that CH can improve various aspects of informal caregiving, such as confidence, depression, and self-efficacy, through the provision of multiple components personalized to each individual. In addition, informal caregivers can benefit from the interaction with other peers or health care professionals [13]. Focusing on the informal caregiver support provided, we found multiple types of technologies in the literature that can be categorized under the umbrella term of CH, including assisted living technology or ambient assisted living technologies, information and communication technology, smart homes, telehealth, telemonitoring, mobile health, and electronic health. Their purpose is to support the informal dementia caregiver in the physical, emotional, and social spheres of their role. As a result, the main outcome of interest of the studies where these technologies are used was an improvement in caregiver’s mental and physical well-being, comparing before and after deployment, as measured by caregiver’s stress, anxiety, depression, burden, and quality of life [14]. A systematic review conducted by Godwin et al [14] on technology-driven interventions for caregivers of PwDs found that these interventions showed positive results in the potential reduction of the caregivers’ burden, improvement in their mental health, increase in their caregiving skills, and increase in competence as a direct benefit from online education, internet-based support groups, computer-mediated interactive voice response systems, and online skill building [14]. This is in line with the current trends of digital interventions for facilitating patients’ and caregivers’ empowerment [15-17]. Another reason for this growing interest for CH in supporting dementia home management is that it can offer a cost-effective alternative to face-to-face care, and it has been progressively integrated into hospitals, physician’s offices, patient homes, and other settings. At the same time, it allows access to personalized health education and support for self-management [18].

A good example found in the literature using a combination of patient home monitoring and informal caregiver support is the ALADDIN (Assisted living of Dementia elDerly INdividuals and their carers) project, which was conducted by Torkamani et al in 2014 [12]. ALADDIN is a computerized platform designed to offer support and information to the carer. It also manages and communicates information related to the PwD and their carers from their home to the clinicians, facilitating distant monitoring. It was tested in a multisite randomized controlled pilot study with 30 community-living informal caregivers of PwDs. The intervention and control groups were assessed at baseline and at 3 and 6 months in terms of burden, depression, and quality of life for the caregiver and in terms of cognitive and disease stage, functional disability, comorbidities, and quality of life for the PwD. The authors reported a significant improvement in the quality of life of the carers in the platform group, with some reduction in carer burden and distress, and that the platform was useful in monitoring the patients and facilitating contact with other professionals. In addition, carers and clinicians rated the access to and use of the ALADDIN platform positively. The success of studies such as this supports further testing of the utility and value of CH in other dementia cohorts and for longer periods and investigating the impact that it can have in the care of PwDs.

### Study Aim

This paper describes the development and implementation protocol of a CH platform system to support informal caregivers of PwDs at home. We believe that a better understanding and more involvement in dementia home care can improve the informal caregivers’ caring experience along with their quality of life and well-being. We want to explore if CH can offer additional support to traditional home care, promoting PwD and caregiver well-being and reducing the amount of burden and stress experienced by the caregiver, which may be translated into better care coping. In addition, we want to gain an understanding of the potential barriers and enablers to adoption by PwD and their informal caregivers of a CH platform to uncover how to change potential negative attitudes toward technology (behavioral change).

## Methods

### Study Design

This paper reports the protocol for a project based on a pilot study conducted by Applied Research in Connected Health, University College Dublin (UCD), between March and June 2014, where technology was deployed to 28 PwD and caregiver dyads for 6 weeks. The pilot project implemented a CH model prototype into dementia home care to investigate its feasibility and acceptability among PwDs and their informal caregivers. The following home-monitoring devices were deployed in the participants’ homes for monitoring the PwD (Multimedia Appendix 1): an Omron blood pressure (BP) monitor (Omron Healthcare, Kyoto, Japan), a Withings Pulse activity tracker (Withings consumer electronics, Paris, France), a Withings scale (Withings consumer electronics, Paris, France), a ResMed Sleep Minder (Biancamed Ltd, Dublin, Ireland), and an Android tablet with the online health platform where all the data collected from the monitoring devices were uploaded and made available for the informal caregivers and the PwD’s health care professionals. Furthermore, the health platform included a section with dementia disease information videos, an online diary section, and a questionnaires section where informal caregivers could periodically fill out some questionnaires regarding the PwD’s ADLs. During the course of the development, the researchers communicated with PwDs and caregivers via video conferencing using the Android tablet provided. Further comprehensive assessments were conducted before and after the CH devices deployment for measuring the informal caregivers’ and PwDs’ quality of life, stress, and depression using scientifically validated questionnaires. Participants were recruited from 2 university hospitals in Dublin that work in collaboration with UCD. Results from its implementation and evaluation in terms of usability and user experience were used to develop the longitudinal project study design that is explained next.

The knowledge acquired from the literature review and the pilot study was applied in the design and development of *Connected HEalth Sustaining home Stay in Dementia* (CHESS), a longitudinal observational mixed methods study where quantitative data will be combined with qualitative data for determining the utility of a CH platform for dementia home care. For this purpose, 3 main objectives have been defined: (1) project feasibility—to evaluate the effectiveness of the CH platform in supporting caregivers of PwDs compared with usual care and caregivers’ ability to cope; (2) impact of CH in dementia home care—in terms of the PwD and their informal caregivers’ physical and mental health, quality of life, and well-being; and (3) users’ feedback—to determine the CH platform’s usability and user experience from the caregivers’ perspectives.

### Participants: Inclusion and Exclusion Criteria

Dyads consisting of a PwD and their informal caregiver living in the community are eligible for this study. For inclusion, the PwD must have a confirmed diagnosis of dementia by a health care professional, have a Mini-Mental State Examination (MMSE) score of 10 or above, have a live-in or dedicated informal caregiver (living with the PwD or spending with them at least 5 days a week, with no minimum hours per day requirement), be 65 years or older, be fluent in English (verbally and written), have a life expectancy of more than 6 months with no hospital admissions in the 3 months before enrolment, have adequate hearing and vision, and not be actively involved in another research study.

Caregivers must be live-in or dedicated informal caregivers, be fluent in English (verbally and written), have adequate hearing and vision, have a life expectancy of more than 6 months, and not be involved in another research study.

In case of not having an internet connection at home, it will be provided to the participants. Therefore, this has not been considered as a selection criterion.

### Ethical Approval, Participants’ Recruitment, and Seeking Consent

Ethical approval from the participating hospitals where recruitment will take place has been granted. Informed consent will be obtained on an individual basis in accordance with legal and ethical guidelines, following careful explanation and provision of an informed consent form for the PwD and a separate informed consent form for the caregiver, detailing their level of involvement. This provided informed consent and cognitive status will be reviewed before each quarterly assessment, giving the PwD and their informal caregiver the right to withdraw at any time. In case the cognitive status decreases under the minimum inclusion score of 10 points or their health declines significantly, they will be asked to abandon the study.

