For this, a sample size calculation was derived using a rule of thumb for 20 observations for each dependent variable, so a sample size of 60 PwD-caregiver dyads is proposed. For the comparison of outcomes between the intervention and the usual care groups, caregiver burden and quality of life will be the primary outcome measure assessed at enrollment and at 6 and 12 months. Acknowledging that the PwD can deteriorate over time with a decline in their cognitive and functional status, we will use scores adjusted for baseline patient dependence and neuropsychiatric symptoms (analysis of covariance, ANCOVA model). We hypothesis a moderate between-groups effect size (*d*=0.5), so with 80% power and alpha=.05, a sample of 64 individuals in the intervention group and 64 in the usual care group is required for the *t* test. Adjusting for ANCOVA by sqrt (1-p2), where the p is the conservative correlation of 0.5 between repeated measures [39], results in a sample of 55 in each group. To account for dropout, 60 PwD-caregiver dyads will need to be recruited for each group. SPSS software (IBM Corp Version 24.0) will be used for this statistical analysis.

Analysis of the qualitative data obtained from the transcribed individual semistructured interviews will be analyzed using content analysis [40]. A guiding codebook will be used for this analysis, which will be created based on the topics examined in the interviews outlined above. The emerged categories will be organized, analyzed, and compared for generating themes. NVivo software version 12 for Macintosh (QSR International) will be used to organize the thematic analysis.

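### The exit rule at MMSE below 10 or significant health decline, read as applying to the dyad, cuts off caregiver-reported primary outcomes according to how the person with dementia (PwD) declines

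*Protocol article*

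**What the plan says.** Under Participants: Inclusion and Exclusion Criteria, the PwD must "have a Mini-Mental State Examination (MMSE) score of 10 or above". Under Ethical Approval, Participants’ Recruitment, and Seeking Consent, the PwD and the caregiver sign separate consent forms, and "This provided informed consent and cognitive status will be reviewed before each quarterly assessment". The exit rule follows: if "cognitive status decreases under the minimum inclusion score of 10 points or their health declines significantly, they will be asked to abandon the study". Significant health decline is not defined there.

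Under Data Analysis, "caregiver burden and quality of life will be the primary outcome measure assessed at enrollment and at 6 and 12 months". Deterioration is foreseen ("Acknowledging that the PwD can deteriorate over time with a decline in their cognitive and functional status"), and the stated response is that "we will use scores adjusted for baseline patient dependence and neuropsychiatric symptoms (analysis of covariance, ANCOVA model"). The same section plans LMMs for the repeated measures and a t test, or nonparametric equivalent, on the month 3 to month 9 change between groups. On attrition it says only "To account for dropout, 60 PwD-caregiver dyads will need to be recruited for each group", with no rate. No caregiver follow-up after the exit rule is described.

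**The concern.** The rule ends follow-up on a variable measured after baseline. MMSE is itself a study outcome, and PwD decline plausibly goes with caregiver burden. If the dyad leaves, burden and quality of life go missing where decline has been greatest. Because the check comes before the assessment, the score at the triggering visit may be lost too.

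Two things are at stake. The first is bias: the section wants months 0 and 12 to show disease progress and quality of life over a year, and the rule removes the fastest decliners from that picture. Groups are self-selected adopters and nonadopters, so equal exit rates cannot be assumed. The second is precision: these exits draw on a small dropout allowance that also has to cover death, nursing home placement and voluntary withdrawal.

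**Working it through.** **1. How the rule reaches the primary outcomes.**
- Entry is at MMSE 10 or more and exit is below 10, so the buffer is zero. A PwD enrolled at 10 exits on a one-point drop, real or retest noise.
- There are four post-baseline checks, at months 3, 6, 9 and 12.
- The Zarit Burden Interview (ZBI) and EQ-5D-5L are answered by the caregiver (Caregiver-Related Outcomes). I read the primary quality of life as the caregiver's. A PwD score of 9 does not prevent the caregiver from answering.

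**2. Size and direction of the bias in an analysis of those who remain.** In one group, let p be the fraction who exit and D the mean change in those who exit minus that in those who stay. The full-group mean change is (1 − p) × stay + p × exit, so the stayers' mean differs from it by −p × D. The bias in the group difference is −(p₁D₁ − p₀D₀). It vanishes only if p × D is equal in the two groups, which self-selection does not secure. The documents give neither p nor D, so no figure can be put on it.

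**3. What the planned analyses do about it.**
- ANCOVA adjusts for baseline dependence and neuropsychiatric symptoms, not for later decline.
- The month 3 to 9 t test uses only dyads with both scores.
- The LMM uses partial follow-up, but is unbiased only if loss is missing at random given the data in the model. The section does not name MMSE over time as part of that model.

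**4. The protocol's sample size, reproduced.** Inputs from Data Analysis: d = 0.5, 80% power, alpha 0.05 (taken as two-sided), correlation 0.5.
- The t test needs 63.77, so 64 per group. Stated: 64.
- 64 × √(1 − 0.25) = 55.4. Stated: 55.
- Implied dropout with 60 recruited: 1 − 55/60 = 8.3%.

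**5. Exits from the MMSE rule alone.** The documents give no entry distribution or rate of decline, so these are assumptions:

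| Assumed entry MMSE | Assumed decline over 12 months | Exit by month 12 |
|---|---|---|
| Bell-shaped, mean 18 or 20, SD 4, truncated to 10–28 | mean 1–3, SD 2–3; month 12 check only, no measurement error | about 1–12% |
| Same | same, with four checks and measurement SD up to 2 | up to about 18% |
| Uniform from 10 to 24–26 | mean 1.5–4, within-person SD 1–2, four checks | about 12–33% |

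The overall range of about 1% to 33% straddles 8.3%. Entry shape drives it: a uniform distribution puts 1/15 to 1/17 of dyads (about 6–7%) exactly at the cutoff.

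**6. Power if loss exceeds the allowance.** Power comes from the noncentral t with effective size n/f per group. The protocol's factor is f = √0.75 = 0.866; the usual ANCOVA variance factor is f = 1 − 0.25 = 0.75.

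| Loss from 60 per group | n left | Power, f = 0.866 | Power, f = 0.75 |
|---|---|---|---|
| 8.3% | 55 | 0.798 | 0.853 |
| 15% | 51 | 0.767 | 0.825 |
| 20% | 48 | 0.742 | 0.801 |
| 30% | 42 | 0.683 | 0.746 |

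To keep 55 per group: 55/0.90 gives 62 recruited, 55/0.85 gives 65, 55/0.80 gives 69 and 55/0.70 gives 79. With the usual factor the need is 64 × 0.75 = 48, and 60 recruited tolerates 1 − 48/60 = 20% loss.

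**The case against.** **The rule may be a consent safeguard.** It follows directly on the review of consent and cognitive status, in a population the protocol calls vulnerable. This stands as a reason to leave PwD participation alone. It is not a reason to stop asking caregivers about their own burden under their own consent. It does limit the remedy: Table 1 lists the NPI-Q, DAD and DEMQOL-Proxy under the PwD, so caregiver consent alone does not clearly cover them.

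**The text does not say that the caregiver leaves.** True. But the enrolled unit is the dyad, the preceding sentence gives both members the right to withdraw, and no caregiver-only follow-up is described. If caregivers are meant to stay, the text should say so.

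**The LMM already uses partial data.** It does, and this softens the point subject to the missing-at-random condition. Detailed missing-data handling belongs to an analysis plan that is not shown, and its absence is not part of this point.

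**Stronger readings that a reader might infer.**
- *That the rule breaks the dropout allowance.* The documents contain no attrition figure, and reasonable assumptions fall on both sides of 8.3%.
- *That 20% loss brings power to 68%.* That is the unadjusted t test at 48 per group. The same test has only 74% at the planned 55, so most of its shortfall from 80% is not due to dropout.
- *That the entry criterion, "have a life expectancy of more than 6 months with no hospital admissions in the 3 months before enrolment", contradicts a 12-month follow-up.* It is a minimum and contradicts nothing.
- *That the caregivers lost are those in greatest need.* This is plausible, but the protocol does not say it.

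**Conclusion.** The point holds as a design weakness. As written, and read as applying to the dyad, the rule makes caregiver-reported primary outcomes missing according to PwD decline. Neither the baseline-adjusted ANCOVA nor the month 3 to 9 t test corrects for this, and the LMM does so only under missing at random. The bias argument needs no simulation. It rests on two premises: that the caregiver leaves with the PwD, and that caregiver outcomes are related to PwD decline.

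The power consequence is conditional. The 8.3% allowance is thin on the protocol's own factor, and it may be exceeded, but that is not demonstrated. A 20% loss would cost about 6 percentage points of power on that factor (0.798 to 0.742). On the usual factor, power would still be about 80%. The change is worth making because outcomes not collected cannot be recovered and collecting them is cheap.

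**What to change.** 1. In the consent section, distinguish ending PwD assessments from leaving the study, and say which member of the dyad the rule covers.
2. When the rule is met, and subject to the caregiver's own consent, continue the caregiver's own instruments (ZBI, EQ-5D-5L, HADS, PSQI) at the scheduled visits to month 12. Continue proxy data about the PwD only if the PwD's consent covers it. PwD participation and use of the package stay with the clinical team.
3. Analyse all dyads in their chosen group with the planned LMM, using every caregiver score collected.
4. In Data Analysis, state the dropout rate behind the step from 55 to 60 and its basis, and reconcile it with the exit rule.

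Cost: consent and protocol wording, and a few additional caregiver interviews at visits already in the schedule. Items 1 to 3 need no extra recruitment. Item 4 would call for more only if the rate, once stated, exceeds what 60 per group can absorb.
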